#### Strategies to improve adherence to interventions {11c}

All the members of the trial team hold Good Clinical Practice (GCP) license from China Food and Drug Administration (CFDA). The Clinical Research Coordinator (CRC) is specialized to inform patients, to follow-up and collect relevant material. There is a statistician to assist the clinical data, which will be collected over 6 months for each patient to follow-up for complications. The principal investigator (PI) will check the process monthly and monitor trial progress. Every quarter, the Clinical Research Center/Office of Quality Management of Shanghai 9th People’s Hospital, School of Medicine, Shanghai Jiao Tong University, will conduct a data audit and verification of the program.

#### Relevant concomitant care permitted or prohibited during the trial {11d}

There is no specific concomitant care or interventions prohibited during the trial. All the patients of the two groups will receive standard perioperative care for their craniofacial fracture.

#### Provisions for post-trial care {30}

The whole surgical team will provide standard postoperative medical care for the participating patients after the trial.

### Outcomes {12}

#### Primary outcome measures

The primary outcome measures will be the accuracy of the key points of surgical areas between preoperational surgical plan and post-operation.

All patients will undergo 3D CT examination 1 week after surgery. The preoperative and postoperative image data will be imported into 3D processing software (Geomagic Control X, 3DSystem, South Carolina). The preoperative and postoperative images will be registered, and the accuracy of the selected fracture points will be measured (Fig. 4). To avoid subjective bias error in measurement, the measurement of this part will be made by the trained engineers who do not participate in the operation and are blinded about the allocation. The measurement will be repeated three times and the average value will be taken as the final data.

**Fig. 4 Fig4:**
[figure not shown]
Accuracy of the key points between preoperational surgical plan and 1-week post-operation 3D CT results. The green indicates the most matched area, and the dark blue and red presents the mismatched area

#### Second outcome measures

The secondary outcome measures will be blood loss, operation time, bone reduction time, hospital time, and rate of complications. The perioperative period outcome will be obtained from medical records. Any complications will be evaluated during the follow-up period (Table 1).

**Table 1 Tab1:** The participant and data collection timeline

	Baseline	Allocation	Operation day	Post-operation	
Timepoint	− Day 7	Day 0	Day 1	7 days	6 months
**Enrolment:**					
**Eligibility screen**	X				
**Informed consent**	X				
**Allocation**		X			
**Interventions:**					
**AR surgery**			X		
**Traditional surgery**			X		
**Assessments:**					
**Accuracy**				X	
**Blood loss**			X		
**Operation time**			X		
**Bone reduction time**			X		
**Hospital time**				X	
**Complications**				X	X
**Adverse event**			X	X	X

#### Primary endpoint

The primary endpoint is the success of post-operative 3D CT examination within seven days. The DICOM data will be transferred to the third-party measuring personnel, and all accuracy outcomes will be evaluated in the three-dimensional software.

#### Second endpoint

The second endpoint will be the success follow-up 6 months after operation. The complications during the follow-up period will be summarized as facial asymmetry, scarring, infection, epistaxis, hardware failure, neurapraxia, facial nerve palsy, temperature sensitivity, blindness, decreased visual acuity, diplopia, lid malposition, ectropion or entropion, corneal exposure or abrasion, enophthalmos, epiphora, and orbital dystopia [6]. These complications will be carefully evaluated by surgeons according to the physical examinations table.

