#### Intervention description {11a}

All patients will undergo a 3D CT scan before surgery (LightSpeed 16, GE, Milwaukee), and the data will be stored in DICOM format. All the digital material will be imported into the corresponding processing software (Mimics 21.0, Materialise, Belgium). In the intervention group, two marker plates will be designed based on the coronal incision that can be fixed on the corresponding bone structure with fixation nails to simultaneously track the fracture block and the whole craniofacial bone (Fig. 2). To ensure the real-time tracking of the markers by the camera, the two-sign plate complexes will be positioned in a parallel arrangement two cm away from the bone surface and oriented as parallel as possible to the coronal surface of the skull (Fig. 3). All marker complexes are obtained using 3D printing (ProJet 660 Pro, 3D Systems, South Carolina) and sterilized before surgery. HoloLens was selected as the hardware support (HoloLens, Microsoft, Washington), and the selected development platform was Unity, written in C# language (Unity, Microsoft, Washington). Tracking will be performed through the Vuforia SDK, which stores the feature points of the logo board in the Vuforia engine database in advance. The video camera of HoloLens is used to track the environment, and the system will continually extract original features from the environment and match them with the template in the database. When matching is successful, the system triggers the display of the model in the set position, which is fixed with the position of the marker board, so the tracking frame rate was guaranteed.

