#### Criteria for discontinuing or modifying allocated interventions {11b}

The criteria for discontinuing or modifying include the malfunction of AR system, surgical accident, and any situation that make the surgeon need to finish the surgery as soon as possible. The demographic data of the patients who meet those criteria will still be collected.

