### Data collection and management

#### Plans for assessment and collection of outcomes {18a}

The preoperative and postoperative image data will be imported into 3D processing software (Geomagic Control X, 3DSystem, South Carolina). The pre- and postoperative images will be registered, and the accuracy of the selected fracture points was measured.

The primary outcome measures will be the accuracy of the key points of surgical site between the preoperational surgical plan and post-operation outcome. The post operational CT will be within 7 days after surgery, and this is the key outcome for the effectiveness of AR technology.

For security measures including intraoperative blood loss, operation time, bone reduction time, hospital time, possible blood transfusion, and rates of complications, it will be arranged for surgeons to record relevant information after surgery within the follow-up period.

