#### Adverse event reporting and harms {22}

According to the published literature on the application of AR in other kinds of surgeries, there is no reported adverse event related to this technique. The clinical doctor in the team will record and provide medical care if any complications occur in either group within the follow-up duration and report it to the ethical committee in a week.

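### The only event-type safety outcome, the complication rate, leaves out AR malfunction, surgical accident and early termination, and the adverse events scheduled on the operation day are not listed as an outcome

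*Protocol article*

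**What the plan says.** The Abstract and the Background section give efficacy and safety of the AR system as the purpose. The Abstract's Discussion paragraph says both will be clarified by accuracy, blood loss, operation and reduction times, hospital stay and complication rates.

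- **Second outcome measures** lists blood loss, operation time, bone reduction time, hospital time and rate of complications. It adds that any complications will be evaluated during follow-up.
- **Second endpoint** describes how complications are summarised: "The complications during the follow-up period will be summarized as facial asymmetry, scarring, infection, epistaxis, hardware failure, neurapraxia, facial nerve palsy, temperature sensitivity", then nine further items, mainly ocular. It adds: "These complications will be carefully evaluated by surgeons according to the physical examinations table".
- **Table 1** marks Complications at 7 days and 6 months only. A separate row, "Adverse event X X X", covers the operation day, 7 days and 6 months.
- **Section {11b}**: "The criteria for discontinuing or modifying include the malfunction of AR system, surgical accident". It also covers circumstances that force the surgeon to finish quickly. For these patients it says only that demographic data will still be collected.
- **Section {11a}**: in the AR arm two marker plates are "fixed on the corresponding bone structure with fixation nails to simultaneously track the fracture block and the whole craniofacial bone".
- **Section {18a}**, repeated in section {19}, gives as security measures "intraoperative blood loss, operation time, bone reduction time, hospital time, possible blood transfusion, and rates of complications".
- **Section {22}** states the duty of the team's doctor as "record and provide medical care if any complications occur in either group within the follow-up duration and report it to the ethical committee in a"; the time limit is one week.

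**The concern.** For a new intraoperative device, part of the safety question is whether the device fails during the operation, whether the operation has to be altered or cut short, and whether an accident occurs. The protocol anticipates such events but treats them only as reasons to discontinue or modify the intervention. The one event count that it plans to compare between arms is a set of post-operative clinical findings common to any zygomaticomaxillary repair, assessed by physical examination at follow-up. A lost tracking display or an abandoned AR procedure would not be found by such an examination.

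At stake is the completeness of the safety statement. Malfunction of the AR system can occur only in the AR arm. Leaving that class out of the reported safety outcome can therefore only make AR look the same or better, never worse. The protocol's Discussion also says the trial should inform a definitive trial, and counts of malfunction and early termination would be useful there.

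**Working it through.** The protocol states no figure for safety events. Its power figures concern the accuracy outcome and have no bearing here, so the main check is to set the sections against each other.

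**Step 1. Where each event class appears**

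| Event | Secondary outcomes | Second endpoint list | Table 1 | Elsewhere |
|---|---|---|---|---|
| Post-operative clinical complications | yes, as a rate | yes, 17 items or item pairs | 7 days, 6 months | {18a}, {19}, {22} |
| Adverse events | no | no | operation day, 7 days, 6 months | heading of {22}; its rule says complications |
| AR malfunction | no | no | no | {11b} only |
| Surgical accident | no | no | no | {11b} only |
| Forced early finish | no | no | no | {11b} only |
| Blood transfusion | no | no | no | {18a}, {19} |

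The {11b} events could be recorded only through the adverse-event row, and nothing says that they count as adverse events. That row leads to no listed outcome. Because Table 1 gives complications and adverse events separate rows with different time points, the two terms cannot be taken as synonyms.

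**Step 2. What one event is worth**

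Input: 22 patients allocated 1:1 (Trial design, Sample size), so 11 in the AR arm. One event is 1/11 = 9.1 percentage points. Exact (Clopper-Pearson) 95% intervals:

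- 0/11: 0 to 28.5% (upper limit 1 − 0.025^(1/11) = 0.285)
- 1/11 = 9.1%: 0.2% to 41.3%
- 2/11 = 18.2%: 2.3% to 51.8%

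**Step 3. Could such an event plausibly occur?**

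The protocol gives no malfunction rate, so p is an assumption. The chance of at least one event in 11 is 1 − (1 − p)^11:

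- p = 5%: 1 − 0.95^11 = 43%
- p = 10%: 1 − 0.90^11 = 69%
- p = 20%: 1 − 0.80^11 = 91%

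**Step 4. Would the planned test change?**

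Fisher's exact test at 11 v 11 gives P = 0.48 for 2 v 0, 0.090 for 4 v 0 and 0.035 for 5 v 0. A few omitted events would not alter significance. The safety information from this trial is descriptive, so its value depends on which categories are shown.

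**The case against.** The strongest case on the other side is that this is a condensed article. Adverse-event definitions, device categories and by-arm safety tables commonly sit in the full protocol, the case-report form or the analysis plan. The text also speaks of any complications in two places and schedules adverse events on the operation day. Much of this stands, and it rules out several stronger readings.

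- A reader might infer that AR malfunctions and accidents will go uncounted. The documents do not show that: the operation-day adverse-event row is a route for recording them. The gap is that the row is not tied to these events or to any outcome.
- A reader might infer that the protocol names marker-plate harms and then ignores them. Section {11a} describes the plates and names no harm. Some consequences could fall under infection, scarring, nerve injury or hardware failure, a term the protocol does not define.
- A reader might infer that intraoperative harm is invisible. Blood loss and operation time are secondary outcomes and would reflect part of it.
- A reader might infer that intraoperative accidents are exempt from ethics reporting, or that {11b} patients are dropped. Section {22} is loosely worded but exempts nothing. Section {11b} does not say that other data are discarded, and section {20c} sets an intention-to-treat analysis.
- A tracking failure that harms nobody is a technical failure, not a complication. That is fair, and it argues for reporting device events separately rather than pooling them with clinical sequelae.

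The objection does not remove the mismatch in what the article does state. It fixes the outcome list, the complication list and the schedule, and these do not cover the events in {11b} or the transfusion measure in {18a} and {19}.

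**Conclusion.** The point holds in this form: the complication rate is the only event-type safety outcome. It is summarised as post-operative clinical items and scheduled only after surgery, so it does not include the AR malfunction, surgical accident and early termination that the protocol foresees. Adverse events are scheduled from the operation day but are not an outcome, the reporting rule names only complications within follow-up, and transfusion is listed inconsistently.

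The size cannot be fixed from the documents. Each event is 9.1 points on an 11-patient arm. If two AR patients had only device or procedural events, the complication rate would read 0/11 while 2/11 had such an event; those counts are an illustration. The 43% to 91% chance of at least one malfunction rests on assumed rates of 5% to 20%. No stated figure and no planned significance test changes. The correction is worth making because safety is a stated aim and the change is cheap.

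**What to change.** 1. In Second outcome measures, add adverse events from the operation day to 6 months as a secondary safety outcome.
2. Keep the complication rate under Second endpoint as it is. Separately, report by arm, with counts and exact confidence intervals: navigation or AR malfunction or loss of tracking, including any marker-plate problem; conversion or early termination of the allocated procedure; surgical accident; and transfusion. Wording the first category for navigation generally lets it apply to the optically tracked control arm as well. Do not merge these categories with the clinical complications into one composite.
3. In section {11b}, state that outcome and safety data, not only demographic data, are kept for patients who meet the criteria.
4. Reconcile Second outcome measures, Table 1 and sections {18a}, {19} and {22}, so that transfusion is listed consistently and operation-day adverse events fall under the reporting rule.

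The cost is protocol wording and a few extra form fields. The operation-day adverse-event row already exists, so no new visit or procedure is needed. The one downside for the sponsor is that the AR safety profile may look less favourable.

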### Participant timeline {13}

The participant timeline is shown in Table 1.

### Sample size {14}

This experiment is a single-center prospective randomized controlled trial. Because this kind of experiment has not been carried out previously, the calculated number of samples mainly refers to the previously related published literature [20–24]. With the approval of the ethics committee, the number of patients in each group needs to be 10 for the primary outcome to be statistically significant; meaning a total of 20 patients is needed. The estimated primary outcome of experiment team is 1.5 to 1.6 ± 0.3 mm, while the controlled team value is 2 ± 0.3 mm according to our previous clinical experience. Given the sample size with 10 patients in each group, it achieves 80.491% power to reject the null hypothesis of equal means when the population mean difference is 0.4 with a standard deviation for both groups of 0.3 and with a significance level (α) of 0.050 using a two-sided two-sample equal-variance *t*-test. This sample size achieves 94.081% power to reject the null hypothesis of equal means when the population mean difference is 0.5 with a standard deviation for both groups of 0.3 and with a significance level (α) of 0.050 using a two-sided two-sample equal-variance *t*-test. To allow for a 10% potential dropout rate, the target sample size of this study will be set to 22.

### Recruitment {15}

This trial is going to be performed in Shanghai 9th People’s Hospital, School of Medicine, Shanghai Jiao Tong University, which is an academic hospital. This hospital is well-known for its plastic and reconstruction surgery and there is a great amount of craniofacial fracture patients having surgery annually which guarantees the targeted number of participants will be enrolled.

### Assignment of interventions: allocation

#### Sequence generation {16a}

In this randomized controlled study, **t**he permuted block randomized assignments list (1:1) has been used for grouping. One group is designated the control team and the other group was designated the experimental team. The random distribution list is developed and provided by a research statistician.

#### Concealment mechanism {16b}

All the parameters of the random distribution list and the random list itself were considered part of the blinded background and were stored in sealed envelopes. Before the blind is uncovered, all patients participating in the trial are kept confidential. Specific ID numbers are adopted. The identifiable information and study data is separated to ensure that the measurers are blind.

During the trial, the operators are unable to design the blind method because he knew which way to use the intervention. Neither the enrolled patients nor the data measurer knew which group the patients were assigned to as part of a single blind trial.

#### Implementation {16c}

First, the investigators in the trial team will take responsibility of enrolling the participants who fulfill the inclusion criteria and get the consent. Then, the research statisticians conduct the randomized allocation and sent the randomized number of the patient. The surgeons will perform the surgery for the patient with or without the AR system according to the allocation. And the engineer who is blinded about the allocation measure the primary outcome.

### Assignment of interventions: blinding

#### Who will be blinded {17a}

The operator is unable to design the blind method because he knew which way to use the intervention. The enrolled patients and the data measurer do not know whether they are undergoing surgery in the augmented reality assisted mode and conducted a single blind trial.

#### Procedure for unblinding if needed {17b}

This is a single blind trial, only the patients and measurer are blinded, and there is no circumstance that they need to be unblinded.

### Data collection and management

#### Plans for assessment and collection of outcomes {18a}

The preoperative and postoperative image data will be imported into 3D processing software (Geomagic Control X, 3DSystem, South Carolina). The pre- and postoperative images will be registered, and the accuracy of the selected fracture points was measured.

The primary outcome measures will be the accuracy of the key points of surgical site between the preoperational surgical plan and post-operation outcome. The post operational CT will be within 7 days after surgery, and this is the key outcome for the effectiveness of AR technology.

For security measures including intraoperative blood loss, operation time, bone reduction time, hospital time, possible blood transfusion, and rates of complications, it will be arranged for surgeons to record relevant information after surgery within the follow-up period.

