#### Data management {19}

The preoperative and postoperative image data will be imported into 3D processing software (Geomagic Control X, 3DSystem, South Carolina). The pre- and postoperative images will be registered and the accuracy of the selected fracture points measured.

The primary outcome measures will be the accuracy of the key points of surgical site between the preoperational surgical plan and post-operation outcome. The post operational CT will be within 7 days after surgery, as the key outcome for the effectivity of AR technology.

For security measures including intraoperative blood loss, operation time, bone reduction time, hospital time, possible blood transfusion, and rates of complications, this team will arrange surgeons to record relevant information after surgery within the follow-up period.

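### Complications are judged, and safety measures recorded, by surgeons not stated to be blinded, which exposes the safety comparison to detection bias; who records what also needs reconciling

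*Protocol article*

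**What the plan says.** All references are to the protocol article.

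- **Recorder.** Plans for assessment and collection of outcomes {18a} lists the measures concerned, "For security measures including intraoperative blood loss, operation time, bone reduction time, hospital time, possible blood transfusion, and rates of complications", and then says "it will be arranged for surgeons to record relevant information after surgery within the follow-up period". Data management {19} repeats the rule: "this team will arrange surgeons to record relevant information after surgery within the follow-up period".
- **Judge of complications.** Second endpoint gives a list that includes facial asymmetry, scarring and enophthalmos, and adds: "These complications will be carefully evaluated by surgeons according to the physical examinations table".
- **Blinding.** Who will be blinded {17a} says of the surgeon: "The operator is unable to design the blind method because he knew which way to use the intervention". Procedure for unblinding {17b} says "only the patients and measurer are blinded". Implementation {16c} ties the measurer to one task: "the engineer who is blinded about the allocation measure the primary outcome".
- **Source.** Second outcome measures says: "The perioperative period outcome will be obtained from medical records". Table 1 places blood loss, operation time and bone reduction time on the operation day.

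**The concern.** The trial sets out to evaluate safety as well as efficacy, and the safety half rests on these secondary measures. Under Primary outcome measures, the authors use blinded engineers outside the operation specifically to keep subjectivity out of a software measurement. Nothing comparable protects the clinical examination, which is the more subjective of the two.

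A surgeon who knows that AR was used may look for, or call, mild asymmetry or a poor scar differently between the arms. Visually estimated blood loss, and the moments taken as the start and end of bone reduction, are open to the same influence to a lesser degree. There is also a stated prior expectation of safety: Adverse event reporting {22} notes that no AR-related adverse event has been reported, and Interim analyses {21b} foresees no serious one. A later analysis plan cannot repair data collected this way.

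**Working it through.** **1. The plan's own figure, and whether it is affected.** Sample size {14} gives a difference of 0.4 or 0.5 mm, SD 0.3 mm, 10 per group and two-sided alpha 0.05. For the equal-variance t-test with 18 degrees of freedom, the noncentrality is (difference/SD) x sqrt(n/2):

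- 0.4 mm: (0.4/0.3) x sqrt(5) = 2.98, power 80.491%
- 0.5 mm: (0.5/0.3) x sqrt(5) = 3.73, power 94.081%

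Both stated figures reproduce. They concern CT accuracy, which blinded engineers measure, so this point does not touch them.

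**2. Who is blinded, outcome by outcome.**

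| Outcome | Recorder or judge | Stated as blinded? | Room for judgement |
|---|---|---|---|
| CT accuracy (primary) | Engineers outside the operation | Yes | Small |
| Examined complications | Surgeons | No | Large for asymmetry, scarring, enophthalmos |
| Blood loss | Surgeons | No | Some, if estimated |
| Bone reduction time | Surgeons | No | Some, at start and stop |
| Operation time, hospital time, transfusion | Surgeons | No | Little; can be checked against routine records |

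The article does not say that the recording surgeon is the operator. Since {17b} confines blinding to patients and measurer, it makes no difference: no clinician is stated to be blinded.

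**3. Who records what, and from which source.**

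- Second outcome measures: medical records, for perioperative outcomes
- {18a} and {19}: surgeons, after surgery
- Strategies to improve adherence {11c}: the coordinator follows patients up and collects material
- Composition of the coordinating center {5d}: trained investigators handle clinical data collection
- Adverse event reporting {22}: the team's clinical doctor records complications

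Nothing says which of these prevails when entries differ.

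**4. What differential recording could do.** The documents give no complication rate and no detection rate, so every input here except the arm size and the test is an assumption. Take 11 per arm, the same true rate p in both arms, complete recording in controls, and a fraction s of complications recorded in the AR arm. The spurious risk difference is p x s - p. The chance of p < 0.05 (either direction) is summed exactly over all binomial outcomes with Fisher's exact test, the test the plan names.

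| p | s | Spurious difference | Chance of p < 0.05 |
|---|---|---|---|
| 40% | 100% | 0 | 1.6% |
| 40% | 75% | -10 points | 2.8% |
| 40% | 50% | -20 points | 7.4% |
| 40% | 25% | -30 points | 19.1% |
| 20% | 50% | -10 points | 1.7% |
| 60% | 50% | -30 points | 16.5% |

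The estimate can be distorted substantially, while false significance stays uncommon unless under-recording is severe or complications are frequent.

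**The case against.** The operator cannot be blinded, and the point does not ask for it. Complications come from a fixed list with an examination table, and data are audited quarterly. These safeguards are real and give some structure, but none of them conceals the arm from the person judging.

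Four stronger readings are tempting, and the article supports none of them:

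- **That surgeon recording contradicts the medical-records source.** Surgeons ordinarily write part of the medical record, so both statements can be true. They are unreconciled, not incompatible. Table 1 already schedules blood loss and the operative times on the operation day, so the reference to the follow-up period may be meant mainly for complications.
- **That every secondary outcome is biased in favour of AR.** Operation time, hospital time and transfusion are largely objective, although discharge or transfusion decisions by staff aware of the arm could still be influenced. Neither the presence nor the direction of bias can be shown in advance; what is shown is a risk.
- **That the surgeons have a stake because they built the system.** Objectives {7} refers to a previously developed AR system without saying who developed it.
- **That one changed call, 1/11 = 9.1 percentage points (two, 18.2), measures the bias.** That is only the granularity of an 11-patient arm.

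Exact definitions of when bone reduction starts and stops may stand in the full protocol; their absence from an article is not held against it.

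It is also fair that the coordinator is not stated to be blinded. Having the coordinator take down the patient's report does not create a blinded examiner. The patient's own report is nevertheless a blinded source, since patients are stated not to know their arm.

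**Conclusion.** The point holds in a limited form. The article states, rather than merely omits to exclude, that surgeons judge complications and record the other safety measures, and it confines blinding to patients and the CT measurer. The safety comparison is therefore exposed to detection bias, mainly in examined complications and less clearly in estimated blood loss and bone reduction time.

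The size cannot be taken from the document. With the assumed 40% true rate and a quarter to three quarters of AR-arm complications unrecorded, the spurious difference runs from -10 to -30 points. The primary outcome and power are unaffected. Separately, the sections on recorder and source need reconciling. This is a worthwhile, inexpensive improvement to the secondary and safety data and does not undermine the main result.

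**What to change.** 1. Reconcile {11c}, Second outcome measures, {18a}, {19}, {5d} and {22} so that each measure has one source and one responsible role:
   - blood loss, operation time and transfusion from the contemporaneous anaesthesia and operating-room record;
   - bone reduction start and stop logged during surgery, on the day Table 1 already schedules;
   - hospital time from the admission record.
2. At the existing 7-day and 6-month contacts, have the coordinator record the blinded patient's own report of complications on a fixed form before the surgeon examines. Report it alongside the surgeon's findings.
3. State in the protocol and the trial report that surgeon-examined complications were assessed without blinding.

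**Cost.** Protocol wording and one short form completed by existing staff; no additional assessor. Signs found only on examination, such as enophthalmos, remain unblinded. Trial status shows recruitment from April 2019, so a change made mid-trial leaves earlier patients recorded under the previous method. The date of the change must then be reported.
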